##### Longitudinal Prospective Cohort

This cohort (n=800) will be used for prospective assessments of children’s vaccination records during their first year of life. Eligible participants will be pregnant women in their last trimester of pregnancy, aged ≥15 years, residing in the sampling area, and expected to reside in the sampling area until the child reaches age 1 year.

Before recruiting this cohort, CHWs, with help from local key informants (eg, village leaders, health care providers, and traditional birth attendants) will compile a list of pregnant women residing in each cluster. The lists will be randomized, and pregnant women will be approached by the research team for eligibility determination, informed consent, and enrollment until 10 pregnant women from each cluster are enrolled into the study. One additional eligible woman will be enrolled from each cluster during each prospective enrollment round to account for loss to follow-up (refer to the *Retention* subsection).

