### Intervention Activities

Figure 1 describes the sequence of intervention activities. Pregnant women, enrolled in their third trimester, will receive a home visit from a CHW before the birth of their child, be registered with the Chanjo Kwa Wakati digital health system, and receive an individualized knowledge intervention to screen and counsel for common knowledge gaps and concerns about routine childhood vaccinations. After the birth of the child, the mother will receive individualized SMS text message reminders for upcoming vaccinations, messages aimed at mitigating persistent vaccination knowledge gaps, service notifications (eg, related to stockouts or service nonavailability), and conditional economic incentive offers aimed at encouraging timely vaccinations. CHWs will use the digital health system for work planning, recording vaccination dates and due dates, and following up on missed vaccination appointments and backstop the digital health system with phone calls and in-person visits as needed for vaccination reminders and assessing and addressing mothers’ knowledge gaps.

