### Study Procedures

#### Cluster Randomization

In each district, all eligible health facilities will be assigned random IDs. Random IDs will be generated using a random number generator in Stata (version ≥16; StataCorp LLC) with a fixed seed to ensure reproducibility. In each district, the 10 clusters with the smallest random IDs will be allocated to either the early onset arm (odd ranks) or delayed onset arm (even ranks). Facilities that are not willing to participate or are deemed ineligible will be replaced with the next odd- or even-ranked facility, respectively. If the distributions of key characteristics of clusters (eg, the number of pregnant women/y, the number of births/y, the percentage of home births, vaccination coverage, and the number of days vaccinations are offered each wk) differ significantly between study arms, a covariate-constrained randomization [21,22] approach will be used to maximize the balance of these characteristics across study arms.

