#### Blinding

Owing to the nature of the intervention, there will be no blinding of investigators, implementers (CHWs), data collectors, or participants.

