#### Randomization

If the distributions of key characteristics of clusters vary greatly between the initially specified study arms (based on randomized IDs), a covariate-constrained randomization approach may be used that maximizes the balance across study arms in the distribution of key characteristics of clusters.

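### Round-1 lists of pregnant women appear to be compiled by unblinded community health workers after allocation, so the same-period A2 versus B2 comparison carries a risk of identification bias

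*Protocol article*

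**What the plan says.** All references are to the protocol article.

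- **Who lists.** Under Longitudinal Prospective Cohort, CHWs with help from village leaders, providers and birth attendants "will compile a list of pregnant women residing in each cluster". Then: "The lists will be randomized, and pregnant women will be approached by the research team for eligibility determination, informed consent, and enrollment". Ten women per cluster and round are enrolled, plus one to cover loss to follow-up.
- **When the arm is set.** Under Cluster Randomization, eligible facilities in each district are ranked by random ID, and "the 10 clusters with the smallest random IDs will be allocated to either the early onset arm (odd ranks) or delayed onset arm (even ranks". A facility that declines or proves ineligible "will be replaced with the next odd- or even-ranked facility, respectively". The limitations add that, if cluster characteristics are unbalanced, "a covariate-constrained randomization approach may be used that maximizes the balance across study arms".
- **Who is blinded.** Under Blinding, "there will be no blinding of investigators, implementers (CHWs), data collectors, or participants".
- **Who delivers.** Under Intervention Activities, each enrolled woman "will receive a home visit from a CHW before the birth of their child". Table 2 adds CHW follow-up after each vaccination due date and issue of incentives.
- **What is claimed.** Quantitative Analysis of Intervention Effectiveness says that, because of the randomization, comparing group means estimates the effect without bias. Study Limitations and Adaptations covers enrollment numbers, cluster imbalance, spillover, external events and missing data. It does not mention how participants are identified.

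**The concern.** Cluster randomization balances clusters. It balances the women in them only if they are identified in the same way in both arms. In an early-onset cluster, the round-1 list feeds a group of women whom the CHW will visit, call and follow for about a year. In a delayed-onset cluster it feeds a group who receive usual care. If the CHW knows which applies, the effort put into finding remote or poorly engaged women could differ by arm, and those women plausibly vaccinate late.

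A2 versus B2 is where this matters most. In round 2 both arms receive the intervention, so listing has no reason to differ by arm. In the retrospective cohorts A1 and B1, being listed brings no intervention work in either arm. A difference-in-difference estimate, (A2 − B2) − (A1 − B1), would therefore not subtract out a listing difference confined to round 1. Nor can an analysis recover women who were never listed.

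**Working it through.** **1. Order of events.** The ranking step both selects a cluster and gives it an arm, and a replacement keeps the arm of its rank parity. The arm of a participating cluster therefore exists before its women are listed. A covariate-constrained redraw could come later, but it is tied to cluster characteristics, not to participant lists. No section says when CHWs are told the arm. The absence of any blinding of CHWs, with no exception for the listing stage, makes knowledge at listing the natural reading, but it remains an inference.

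**2. What each safeguard covers.**

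| Safeguard | Protects | Leaves open |
|---|---|---|
| Randomized list order | Choice among listed women | Who is on the list |
| Approach by research team | Hand-picking by CHWs after listing | List completeness; recruiters are unblinded too |
| Local informants help with listing | Reliance on one source | No stated masking of informants |
| Covariates in the accelerated failure time model | Measured differences | Unmeasured differences |

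**3. The plan's own figure.** Statistical Power gives 60 versus 60 cluster-periods of 10, SD 28 days, difference 7 days. Two-sided alpha 0.05 is my assumption, as none is stated. Design effect = 1 + 9 × ICC; SE = 28 × √(2 × design effect / 600); power ≈ Φ(7/SE − 1.96).

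- ICC 0.05: design effect 1.45, SE 1.95, power 0.949 (stated 0.95).
- ICC 0.10: design effect 1.90, SE 2.23, power 0.881 (stated 0.88).

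The stated power reproduces, and this point does not dispute it. For A2 versus B2 alone, with 200 per group, the same formula gives SE 3.37 and 3.86 days.

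**4. Illustrative size.** Bias = (difference between arms in the share of women omitted) × (their extra mean delay). The article gives neither input, so every entry below is an assumption. Results are days in A2 versus B2.

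| Share | 7 days | 14 days | 28 days |
|---|---|---|---|
| 10% | 0.7 | 1.4 | 2.8 |
| 20% | 1.4 | 2.8 | 5.6 |
| 30% | 2.1 | 4.2 | 8.4 |

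Take 10% × 28 days (one planning SD) = 2.8 days. With no true effect, the chance of a significant A2 versus B2 difference rises from 5% to about 13% (ICC 0.05) or 11% (ICC 0.10).

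In the pooled comparison A2 is 200 of 600 intervention children, so a bias confined to A2 is 2.8 × 200/600 = 0.93 days. The false-positive rate is then about 7.7% (ICC 0.05) or 7.0% (ICC 0.10). This dilution holds only if A3 and B3 are not affected in the same way.

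**5. Length of the list.** At the eligibility floor of 100 pregnancies or births a year, spread evenly, about 100 × 3/12 = 25 women are in the last trimester at once, and 11 are enrolled.

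**The case against.** The strongest reply is that no sentence says CHWs know the arm on the day they list. Blinding is ruled out because of the nature of the intervention, which does not settle when the arm is disclosed, and a condensed article may leave the sequence to the full protocol. This stands as far as wording goes: the timing must be presented as inferred.

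Second, the motive is weaker than it may look. Being listed does not put a woman in the caseload. About 11 per cluster and round are enrolled whatever the list length, so leaving women off does not shrink the CHW's work. A reason to leave off distant women could remain, because it affects which 11 are drawn.

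Third, there is mitigation. Several kinds of informant help with the list, all participants are compensated for their time, and the enrollment survey records access barriers, attitudes and sociodemographic data that the model can use. These narrow the risk but do not reach unlisted women or unmeasured differences.

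A reader might go further and infer that A2 versus B2 is biased, perhaps by 40% of the target effect (2.8/7). The documents do not support that. Both inputs are assumed, the range runs from trivial to larger than the target, and the 7 days is powered on the pooled 600 versus 600 comparison, not on A2 versus B2. The direction is also open: keener listing in early-onset clusters could bring in more hard-to-reach women and hide a benefit.

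**Conclusion.** The point holds as a risk built into the described procedure, not as a demonstrated bias. It rests on one firm but unstated inference, that listing follows allocation and that CHWs can know the arm by then. On that reading, the completeness of the round-1 lists is unprotected in the only same-period contrast of treated and untreated children, and cluster randomization alone does not justify the unbiasedness statement. The 2.8 days (A2 versus B2) and about 0.9 days (pooled, if confined to A2) only show scale. If the full protocol already withholds the arm until the lists are closed, the remaining change is to say so and to soften the claim.

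**What to change.** **Main change.** In Longitudinal Prospective Cohort and Cluster Randomization, state that the arm is withheld from CHWs, facilities and recruiters until that cluster's round-1 list has been compiled and locked. Because the arm follows from odd or even rank, the ranks must be withheld as well. Working cluster by cluster is enough and keeps the gap from list to enrollment short, which matters because women are in the last trimester and are to be visited before the birth.

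**Wording.** In Quantitative Analysis of Intervention Effectiveness, make the unbiasedness statement conditional on participants being identified and recruited in the same way in both arms, and name the risk among the limitations.

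**Supporting check.** Report by arm the numbers of women listed, approached, eligible and refusing, with baseline characteristics. This is needed because locking the list does not prevent differential consent once women hear the offer.

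**Cost.** A sequencing rule and a tracking table, with no extra participants and no change of design. The small downside is that intervention training in early-onset clusters must follow list lock. The change has to be in place before round-1 listing starts.

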##### Participants in Qualitative Feedback

This group will be used to obtain feedback on the RE-AIM constructs. Eligible participants will be key informants at the national, regional, or local levels (target: n=12), health providers from participating facilities who are responsible for childhood vaccinations (target: n=40, approximately 1/cluster), CHWs in study clusters (target: n=80, approximately 2/cluster), and women enrolled in the prospective cohort (target: n=60).

To recruit these participants in qualitative work, a combination of purposive and snowball sampling strategies will be used. The numbers of participants represent target numbers; additional participants will be enrolled if saturation is not reached. Key informants, including policy makers, decision makers, and implementers at the national, regional, or local levels (eg, officials from Tanzania’s Immunization and Vaccines Development program as well as regional, district, and local health officials) will be asked to participate in qualitative interviews on implementation factors and to recommend other individuals who can provide relevant information. Health providers who are responsible for childhood vaccinations will be enrolled from participating health facilities. CHWs will be enrolled from participating clusters. Women will be purposively selected from the prospective cohort based on data collected during enrollment or follow-up surveys, study logs, or the digital health system during study implementation.

### Study Design

#### Cluster Randomized Trial Design

Forty rural health facilities and their catchment areas (*clusters*), 20 per region, will be randomized to an (A) early or (B) delayed onset study arm (Figure 2). From each cluster, 3 cohorts of 10 mother-child dyads (1 retrospective cohort and 2 prospective cohorts) will be enrolled into the study. For the retrospective cohort, 400 mothers of children aged 12 to 23 months (10/cluster) will be enrolled as a cross-sectional sample for retrospective assessments of children’s vaccination records during the first year of life. These cohorts, denoted by A1 and B1, will be part of the care-as-usual control group. For the longitudinal prospective cohort, 800 pregnant women in their last trimester of pregnancy will be enrolled during 2 rounds of enrollment (10 women/enrollment round/cluster) for prospective assessments of their children’s vaccination records during the first year of life. These cohorts are denoted by A2, A3, B2, and B3. In the first round of enrollment, 200 (50%) of the 400 prospective participants (those enrolled from early onset clusters; A2) will receive the intervention, and the other 200 (50%) participants (B2) will be part of the care-as-usual control group. In the second round of enrollment, all 400 participants (A3 and B3) will receive the intervention. In total, vaccination uptake and timeliness will be observed for 1200 children (n=600, 50% intervention group children and n=600, 50% nonintervention group children) during their first year of life. The nonintervention group children represent the *care-as-usual* control group in the trial.

The trial design, which analytically resembles a difference-in-difference design, allows for an analysis of the effectiveness of the intervention even in the context of contemporaneous changes in the rate and timeliness of vaccinations at the national level (eg, through national vaccination campaigns or changes in the vaccination schedule).

**Figure 2 figure2:**
[figure not shown]
Design of the 2-arm cluster randomized trial (n=1200).

#### Evaluation Framework

The evaluation of the Chanjo Kwa Wakati intervention will be guided by the RE-AIM framework. Quantitative survey data will be the primary source of information for the analysis of the effectiveness of the intervention. These data will be complemented by study logs, fidelity checklists, and qualitative interviews with Tanzanian key informants, facility-based health workers, CHWs, and mothers to assess the acceptability, reach, and fidelity of Chanjo Kwa Wakati, as well as factors that may inform sustainability and scalability in the future.

### Outcomes Assessments

Vaccination outcomes are described in Table 3. Vaccination coverage and dates will be ascertained for each study child using government-issued vaccination cards, which will be photographed, scanned, or copied and entered by research staff. For the retrospective cohort, the enrollment survey will assess vaccination outcomes for the child; their participation will end after the enrollment survey. Outcome data for the prospective cohort will be collected during an endline survey 12 to 15 months after the birth of the child. All vaccination doses of all vaccination series will be tracked. For women who cannot provide vaccination cards at the time of the survey, consent will be sought to access their children’s paper-based or electronic vaccination records at their local health facility.

**Table 3 table3:** Outcome measures for the cluster randomized controlled trial.

Outcome measure	Type	Source
Timeliness of the third dose of the pentavalent vaccine, Penta3 (number of days delayed)	Primary	Vaccination cards
Timeliness of Penta3 (≤28 days delayed)	Secondary	Vaccination cards
Timeliness of all other vaccine doses recommended by age 1 y (number of days delayed)	Other	Vaccination cards
Coverage of all vaccine doses recommended by age 1 y	Other	Vaccination cards

### Study Procedures

#### Cluster Randomization

In each district, all eligible health facilities will be assigned random IDs. Random IDs will be generated using a random number generator in Stata (version ≥16; StataCorp LLC) with a fixed seed to ensure reproducibility. In each district, the 10 clusters with the smallest random IDs will be allocated to either the early onset arm (odd ranks) or delayed onset arm (even ranks). Facilities that are not willing to participate or are deemed ineligible will be replaced with the next odd- or even-ranked facility, respectively. If the distributions of key characteristics of clusters (eg, the number of pregnant women/y, the number of births/y, the percentage of home births, vaccination coverage, and the number of days vaccinations are offered each wk) differ significantly between study arms, a covariate-constrained randomization [21,22] approach will be used to maximize the balance of these characteristics across study arms.

#### Blinding

Owing to the nature of the intervention, there will be no blinding of investigators, implementers (CHWs), data collectors, or participants.

#### Enrollment

Participants may be enrolled at their homes, health facilities, or other mutually agreed-upon locations. The potential risks and benefits of research participation will be carefully explained during the informed consent process (refer to the *Ethical Considerations* subsection). To maximize the reach of the intervention, participants without mobile phones will be able to designate a vaccine advocate of their choice to receive mobile phone–based messages.

#### Retention

Retention only applies to the prospective cohort. To ensure the retention of study participants, extensive contact information, including the names and mobile phone numbers of both parents, vaccine advocates, and other contacts, as well as expectations for the place of delivery, travel plans after birth, and GPS coordinates of homes will be documented at enrollment. In the event of child death, maternal death, or participant withdrawal, intervention activities related to the mother-child dyad will be suspended, and the dyad will be withdrawn from the study. In the event of child relocation or family travel during study activities, efforts will be made to collect outcomes data for the child using a combination of mobile phone–based surveys; a review of the child’s records at the local health facility; and proxy reports from the father, other legal guardians, or other informants. As the intervention involves local CHWs, for participants relocating outside their cluster for the remainder of the study period, intervention activities will stop after relocation.

### Data Collection

#### Overview

Trained research assistants will conduct enrollment and data collection in Kiswahili. Survey instruments will be developed in English, translated into Kiswahili, and back-translated into English. The development of the surveys will be informed by prior surveys [6,8].

#### Enrollment Survey

All participants will complete an enrollment survey. The survey will last approximately 45 minutes and assess knowledge and attitudes, sociodemographic characteristics of participants and their households, access barriers, digital literacy, residual knowledge gaps, and other correlates of vaccine uptake and timeliness. The mother’s engagement in prenatal care will be assessed via self-report and scanned prenatal care cards. For retrospective participants, the enrollment survey will also assess vaccination uptake and timeliness (Table 3), whereas for prospective participants, extensive contact information will be collected (refer to the *Retention* subsection).

#### Follow-Up Survey

Prospective participants will complete a follow-up survey 12 to 15 months after their child’s birth. The survey will last approximately 30 minutes. The primary purpose of the follow-up survey is to collect data on vaccination outcomes (Table 3). The follow-up survey will include the knowledge intervention that addresses each woman’s vaccination-specific knowledge gaps and assess vaccination attitudes and experiences with vaccine uptake and timeliness during the study period. The follow-up survey will also be used to update information on mothers’ engagement in prenatal care via self-report and scanned prenatal care cards. For intervention group women, the follow-up survey will also assess implementation measures, experiences with the intervention, and the acceptability and perceived efficacy of Chanjo Kwa Wakati.

#### Facility Survey

During the enrollment and follow-up work, we will conduct a survey of the health facility in each cluster. The purpose of the facility survey is to assess the implementation context. The survey will collect service information (eg, information on vaccine stockouts and facility closures), procedural knowledge (eg, vaccination dates, scheduling, and rescheduling), and contact information.

#### Qualitative Data

In-depth interviews (IDIs) will elucidate wide-ranging feedback on all constructs of the RE-AIM framework. IDIs will be conducted by local trained study staff in English or Kiswahili. Study staff will follow a semistructured interview guide. IDIs will be recorded to facilitate transcription and data analysis. Depending on the availability of the participants, IDIs may be conducted by phone or in person. IDIs are expected to last 45 to 60 minutes.

### Statistical Power

The aim 1 cluster randomized trial will include 1200 women, enrolled from 40 different clusters, across 3 distinct enrollment phases, with 10 women enrolled from each cluster in each phase. This equates to k=120 statistical clusters with n=10 women per cluster. Half of these clusters (k=60/120, 50%; n=600/1200, 50%) will be allocated to the intervention arm and half to the control arm. Assuming that the primary outcome—the timeliness of the Penta3 vaccine—has an SD of 28 days, the power of the trial to detect an intervention-related difference of 7 days is 0.95 with an intracluster correlation coefficient of 0.05; the power is 0.88 with an intracluster correlation coefficient of 0.10.

The aim 2 qualitative formative work will yield data from IDIs with key informants (n=12), facility-based health workers (up to n=40), CHWs (up to n=80), and mothers (up to n=60). Prior research suggests that thematic saturation can be achieved with 12 interviews, with metathemes presenting as early as 6 interviews [23-25]. Thus, these proposed sample sizes should be sufficient to achieve thematic saturation of implementation barriers and residual barriers to timely and equitable vaccinations, as well as to identify any regional variation in reasons for delayed vaccinations.

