## Introduction

### Background

Globally, the number of children missing their first dose of the diphtheria-pertussis-tetanus (DPT) vaccine rose from 19 million in 2019 to 25 million in 2021 [1,2]. The vast majority (14.2 million, 78%) of such *zero-dose* children reside in 20 countries, including Tanzania [3]. As in other low- and middle-income countries (LMICs), substantial rural-urban disparities in routine childhood vaccination exist in Tanzania, with vaccination rates being lower in rural areas than in urban areas [4]. Using data from the 2015-2016 Tanzanian Demographic and Health Survey, we demonstrated gaps in vaccination coverage (receipt of each recommended vaccine dose by age 1 y) and timeliness (receipt of each vaccine dose within 28 d of the recommended age) for Tanzanian children [4]. The coverage of the first dose of the pentavalent vaccine (Penta1, which includes antigens of DPT, *Hemophilus influenzae*, and hepatitis B) was 79.4% nationally in this analysis, with the remaining 21% of children classified as zero dose [4]. We documented receipt of the third dose of the pentavalent vaccine (Penta3) in even fewer children (72.7%), suggesting dropouts in the multidose vaccine series. Finally, rural children had lower timeliness of vaccination (47.8% delayed for Penta3) than urban children (24.2% delayed for Penta3). New interventions are needed to reduce the number of children who are zero dose, receive delayed vaccines, or drop out and to close the rural-urban gap in vaccination [4,5]. Such interventions must consider multifaceted barriers to vaccination and variations in the availability of human resources and infrastructure in rural areas.

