### Study Setting

The study will be conducted in 4 rural districts in Mwanza and Shinyanga regions in Tanzania. Both regions have large numbers of unvaccinated or undervaccinated children. The populations of Mwanza and Shinyanga region were estimated to be 3,699,872 and 2,241,299, respectively [18]. In 2022, only 56% of children aged 12 to 23 months in Mwanza region and 32.2% of children in Shinyanga region were estimated to have received all basic vaccinations, including one dose of Bacillus Calmette-Guerin vaccine, 3 doses of polio vaccine, 3 doses of DPT-containing vaccine, and one dose of measles-containing vaccine [19]. Fewer children aged 12-23 month were considered fully vaccinated according to the national vaccination schedule shown in Table 1 (32.8% in Mwanza and 2.5% in Shinyanga) [19]. Notably, 3.3% of children aged 12-23 months in Mwanza and 14.5% in Shinyanga were reported to have received no vaccinations. [19].

**Table 1 table1:** Routine childhood immunizations recommended in Tanzania before age 1 year.

Antigen	Age at vax due date
Bacillus Calmette-Guerin (BCG) and oral polio vaccine (OPV) 0	At birth or first contact
OPV1; pentavalent vaccine comprising antigens of diphtheria, pertussis, tetanus, *Hemophilus influenza* B, and hepatitis B (Penta) 1; pneumococcal vaccine (PCV) 1; and rotavirus vaccine (Rota) 1	6 weeks
OPV2, Penta2, PCV2, and Rota2	10 weeks
OPV3, Penta3, PCV3, and injectable polio vaccine (IPV)	14 weeks
Measles and rubella 1	9 months

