### Data Analysis

#### Quantitative Analysis of Intervention Effectiveness

The primary outcome measure of interest will be a continuous measure of vaccination timeliness, expressed as the delay, in days, between the vaccination due date and the date on which the vaccination was received for the third dose of the pentavalent vaccine, Penta3, due at age 14 weeks (Table 1). The secondary and other outcome measures include the timeliness and coverage of all vaccine doses recommended by age 1 year. Owing to the randomization, a comparison of mean outcomes between participants in the intervention group and those in the nonintervention group yields an unbiased estimate of the effect of the intervention.

To control for variation in sociodemographic characteristics across participants, seasonal effects, and other potential correlates of vaccination timeliness, outcomes will also be analyzed in a multivariable regression framework using accelerated failure time models with the completed vaccination dose as the failure event, age in days describing time to failure, and membership in the intervention versus control groups as the primary covariate of interest.

Robust SEs will be estimated to account for the clustering of observations across mother-child dyads enrolled from the same geographic clusters at the same time.

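### The stated power of 0.95/0.88 counts every enrolled child as having a Penta3 delay; at the 72.7% receipt the protocol cites, the same formula gives about 0.90/0.82

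*Protocol article*

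**What the plan says.** Protocol article, Statistical Power: the 40 facilities and three enrolment phases are treated as 120 cluster-phases, "This equates to k=120 statistical clusters with n=10 women per cluster". Half of them "will be allocated to the intervention arm and half to the control arm", which makes 600 children against 600. The primary outcome is assumed to be one that "has an SD of 28 days, the power of the trial to detect an intervention-related difference of 7 days is 0.95" at an ICC of 0.05, and "the power is 0.88 with an intracluster correlation coefficient of 0.10".

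Protocol article, Quantitative Analysis of Intervention Effectiveness: the primary outcome is timeliness of Penta3, "expressed as the delay, in days, between the vaccination due date and the date on which the vaccination was received". Group means are compared. An accelerated failure time model is planned in addition, to adjust for covariates.

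Protocol article, Background, from the 2015-2016 national survey, with coverage defined as receipt by age 1 year: "We documented receipt of the third dose of the pentavalent vaccine (Penta3) in even fewer children (72.7", the figure being a percentage.

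Protocol article, Study Setting: 56% of children aged 12 to 23 months in Mwanza had all basic vaccinations, while "32.2% of children in Shinyanga region were estimated to have received all basic vaccinations". Children with no vaccination at all were 3.3% and 14.5%.

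Protocol article, Longitudinal Prospective Cohort: "One additional eligible woman will be enrolled from each cluster during each prospective enrollment round to account for loss to follow-up".

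**The concern.** The number of children in the power calculation is not the number the mean-delay comparison can use. A delay that ends on the date of receipt does not exist for a child who never received the dose, and the article itself describes non-receipt as common.

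The provisions that add participants do not address this. A child whose card is available and shows no Penta3 is neither lost to follow-up nor missing a card, so neither the spare woman nor the top-up in the Missing Data subsection is triggered.

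At stake is the accuracy of the power printed for the primary outcome. At ICC 0.10 the type II error would be nearer 18% than the stated 12%. The same count of 10 per cell would also pass unnoticed into any later recalculation.

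**Working it through.** **Inputs.** From Statistical Power: 60 cluster-phases per group, m = 10 children in each, SD 28 days, difference 7 days, ICC 0.05 or 0.10. From Background: Penta3 receipt 72.7%. Assumed: two-sided alpha of 0.05, since none is stated, and equal receipt in both groups.

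**Formula.** Effective number per group: N = 60m / (1 + (m − 1) × ICC). Power = Φ(7 / (28 × √(2/N)) − 1.96).

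**Step 1: reproduce the printed figures with m = 10.**
- ICC 0.05: N = 600 / 1.45 = 413.8; 7 / 1.947 = 3.596; Φ(1.636) = 0.949. Printed: 0.95.
- ICC 0.10: N = 600 / 1.90 = 315.8; 7 / 2.228 = 3.141; Φ(1.181) = 0.881. Printed: 0.88.

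A noncentral t with 118 degrees of freedom gives 0.946 and 0.876. One-sided 0.05 gives 0.974 and 0.933 and does not match. Neither do 20 facilities per arm with 30 children each (0.790 and 0.592); that variant only identifies the formula and is not proposed as the right design calculation. The printed values therefore use all 10 children in every cluster-phase.

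**Step 2: count only children with a delay.** 1200 × 0.727 = 872 children, or m = 7.27 per cluster-phase.
- ICC 0.05: N = 436.2 / 1.3135 = 332.1; 7 / 2.173 = 3.221; Φ(1.261) = 0.896.
- ICC 0.10: N = 436.2 / 1.627 = 268.1; 7 / 2.418 = 2.895; Φ(0.935) = 0.825.

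The t version gives 0.892 and 0.819. Allowing for unequal numbers per cell (binomial, coefficient of variation 0.19) gives 0.893 and 0.819.

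**Step 3: sensitivity to the receipt assumed in both groups.**

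| Receipt | m | ICC 0.05 | ICC 0.10 |
|---|---|---|---|
| 100% (as printed) | 10 | 0.949 | 0.881 |
| 91.1% | 9.11 | 0.937 | 0.867 |
| 72.7% | 7.27 | 0.896 | 0.825 |
| 65% | 6.5 | 0.871 | 0.801 |
| 60% | 6.0 | 0.851 | 0.782 |

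The 91.1% is an upper limit for the study regions from Study Setting: 100 − (3.3 + 14.5)/2, weighting the regions equally because each supplies 20 clusters. With 72.7% in controls and an assumed 85% in the intervention group, power is 0.911 and 0.840.

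**The case against.** **The arithmetic is right on its inputs.** This stands: the printed figures follow from what the paragraph assumes. The fault lies in an input, the number of children with an outcome value.

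**The 72.7% is not an estimate for this trial.** This also stands. It is national, dates from 2015-2016, and is never applied to the trial's children. Half of them receive an intervention meant to raise coverage as well as timeliness. Against that, the figure is not specific to rural areas and Study Setting describes low-coverage regions, so true receipt could lie on either side.

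**The accelerated failure time model can keep children without the dose as censored.** True, and the full analysis plan may say how they enter the primary comparison. But the printed power is for a difference in days against an SD in days. No event fraction or time ratio is given, so it does not describe that model.

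Four stronger readings are tempting and are not supported:
- A reader might infer that the spare woman is the plan's only reserve. The Missing Data subsection continues enrolment when cards are missing for more than 10% of the cross-sectional sample, and the limitations section allows additional clusters. These exist; they are simply not triggered by non-receipt.
- A reader might take the average share with all basic vaccinations, (56 + 32.2)/2 = 44.1%, as likely Penta3 receipt. That measure also requires BCG, three polio doses and measles vaccine, so it is only a floor.
- A reader might infer that power collapses if children without Penta3 are given a delay running to age 1 year. The article assigns no such value, and holding the difference at 7 days on so stretched a scale would be arbitrary, since any gain in coverage would itself move the mean.
- A reader might infer that the trial is underpowered. At 72.7% this formula still gives more than 0.80 at both ICCs, and the article states no power target that is missed.

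**Conclusion.** The point holds as a sample-size assumption that does not fit the outcome being powered. On the plan's own formula, with two-sided 0.05 and 72.7% receipt assumed in both groups, power is about 0.90 at ICC 0.05 and 0.82 at ICC 0.10, a loss of 5 to 6 points. The loss shrinks to between 1 and 1.5 points if receipt is near 91%. At ICC 0.10 power falls below 0.80 only if receipt is under about 65%. The direction does not depend on which value is right: any receipt below 100% lowers the stated figures for the comparison of mean delays. The effect is modest, and it concerns the accuracy of the stated power, not the validity of the estimate.

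The values 0.90 and 0.82 are not the trial's true power either. The formula treats the 120 cluster-phases as independent, although each facility contributes three of them. The check here isolates the effect of non-receipt alone.

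**What to change.** In Statistical Power, replace 10 children per cell with the expected number who will have a dated Penta3 dose. State the assumed receipt, its source and a range, and restate the power across that range. Allow receipt to differ between groups if a coverage gain is expected.

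Use these counts as an input to any recalculation for the actual design, and do not print 0.90/0.82 as the final answer.

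If children without Penta3 are to stay in the primary comparison, for example as censored in the accelerated failure time model, compute power for that analysis with its own event fraction or SD and its own effect size, not with an SD of 28 days and a difference of 7 days.

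The cost is a short recalculation and a few lines of text, and a less favourable stated power. Enrolment and procedures do not change.
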